**Inclusion criteria:**
Admitted to the ICU >24 hoursAged >18 yearsEnglish or French speaking
**Exclusion criteria:**
Delirium (Group A only)Lack an available fingerSevere peripheral vascular disease affecting the upper limbsUncontrolled cardiac arrhythmia (eg, atrial fibrillation)Pacemaker with paced rhythmSevere edema in upper limbsHypoperfusion state or shock and receiving norepinephrine (>14 mcg/min) or equivalent vasopressors to maintain a systolic blood pressure >90 mmHg or a mean arterial pressure >65 mmHgAgitated (Richmond Agitation Sedation Scale +1 to +4)PsychosisCognitive deficits (eg, Alzheimer)Positive for Clostridium difficilePregnancy

### Recruitment and Consent Procedures

ICU patients are screened for eligibility by the research staff in collaboration with the medical and nursing team. Potentially eligible ICU patients able to self-report and consent, if they agree to participate, are assigned to Group A. Other potentially eligible ICU patients unable to self-report and consent are assigned to either Group B or C. According to Article 21 of the Quebec Civil Code for minimal risk studies, a significant person qualified to consent to care required by the state of health of the person of full age is asked to provide consent on their behalf for the research study.

Group A: Potentially eligible ICU patients able to self-report are approached for participation by their responsible nurse or physician. If interested, the research staff provides information about the study to the patient and obtain written informed consent.

Group B and Group C: For potentially eligible ICU patients unable to self-report, the person qualified to consent on their behalf is approached by their responsible nurse or physician. If interested, the research staff provides information about the study to the significant person and obtain written informed consent. If a patient participant who was previously unable to consent regains the ability to consent at any time, the research staff provides them with the informed consent form, allowing them to decide on their continued participation in the study. If a patient participant decides to withdraw from the study and requests their research data be removed, all collected information will be deleted.

### Study Procedures

Before starting data collection, the group assignment of the participant is confirmed by the research staff. Then, the research staff sets up the NOL device at the bedside, places the finger probe on the participant’s finger, and proceeds with calibration (requires less than 5 minutes). The screen of the NOL device is faced away from the patient and family members present in the room to reduce potential bias. Research staff also installs a video camera on a tripod at the foot of the bed to capture the face and the upper body in order to allow for interrater reliability examination of CPOT scores with another trained research staff not present at the bedside.

Participants are assessed at rest before, during, and 15 minutes after nonnociceptive and nociceptive procedures that are part of ICU routine care. Whenever possible, 15 minutes postprocedure are respected to allow for the resolution of the release, reaction, and elimination of stress hormones (ie, epinephrine and norepinephrine) and stress-activated responses that may be present following noxious stimulation [33]. The nonnociceptive procedures are ideally performed prior to nociceptive procedures and include soft touch (ie, research staff touching the patient’s arm for 1 minute) and cuff inflation for blood pressure measurement (NIBP), which were empirically shown to be painless in previous studies [34], including our pilot NOL studies [26,27]. In the sequence of nonnociceptive procedures, soft touch is performed first and cuff inflation last. Then, the goal is to observe up to two nociceptive procedures per participant (Textbox 2). Nociceptive procedures are selected according to the standard care required by the patient’s condition. These procedures do not involve mobilizing the patient out of bed, as important movements may introduce artifacts in the NOL data. When possible and as required by the patient’s condition, participants are also assessed before and 15 minutes postadministration of a breakthrough dose of an opioid such as fentanyl, morphine, or hydromorphone through a parenteral route (mainly through intravenous or subcutaneous routes) to capture onset or peak of action. The decision to administer an opioid is made as per local practice and based on an assessment performed by the ICU nurse or physician. Within a window of 48 hours after obtaining informed consent, a total of 10 to 12 time points of data collection is completed with each participant during their ICU stay (Table 1).

The NOL index is continuously monitored during the data collection time period, and values are extracted in a standardized manner as done in previous clinical studies for NOL data analysis purposes [24-27]. CPOT assessments (one-minute observation or duration of the procedure) are performed on participants from Groups A and B by research staff, and then conscious patients able to self-report (Group A) are asked to provide their self-report of pain intensity at each time point. Video recording is stopped before participants provide their self-report to avoid possible bias by the research staff, who will view the videos for CPOT scoring at a later time. Finally, demographic and clinical information is extracted from the participants’ medical files. At the end of data collection, the study equipment (ie, video camera, tripod, NOL device, and keyboard) is disinfected according to the prevention control infection procedures of each institution before being used for another patient.

List of nociceptive and nonnociceptive standard care procedures in the intensive care unit.

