**Figure 1 figure1:**
[figure not shown]
Nociception Level (NOL) index.

The PMD-200 device allows the documentation of each event (ie, beginning and end time of rest and procedure assessment) or any contextual information (eg, interruption during a procedure), which is facilitated with the use of a wireless keypad. All NOL data are electronically collected every 5 seconds by the PMD-200 monitor.

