### Data Analysis

SPSS software (version 29; IBM) and SAS (version 9.4; SAS Institute) will be used for data analysis. Descriptive statistics will be computed to characterize the study samples and outcomes. The NOL signal quality will be checked for all enrolled patients to ensure the accuracy of the data. As done in previous studies, NOL values will be averaged within 15 seconds before and after the peak value obtained after the start of each nonnociceptive procedure (7 NOL values total around the peak for soft touch and NIBP) and nociceptive procedure. In addition, NOL values will be averaged over a 1-minute period at rest before and after the procedure. CPOT scores will be obtained independently by 2 trained raters, one at the bedside and one who will view the patient videos at a later time. Intraclass correlation coefficients (ICC) will be calculated between the CPOT scores of both raters during procedures. ICC>0.80 will confirm excellent interrater reliability [28].

For objective 1 (criterion validation), the receiver operating characteristic (ROC) curve [43] will be performed to examine the ability of the NOL to adequately classify patients with pain. In patients able to self-report (Group A), an established pain intensity score >4 based on participants’ self-reports as the reference standard criterion indicating moderate to severe pain will be used [10,44]. This criterion is also commonly used in practice to support clinical decisions in the administration of opioids. A ROC curve will be obtained for each nociceptive procedure (a total of 2 procedures per patient). In patients unable to self-report but in whom behaviors can be observed (Group B), we will use the determined CPOT score >2 as the alternative reference criterion, which is associated with the presence of moderate to severe pain [44]. Again, for Group B, a ROC curve will be obtained for each nociceptive procedure (total of 2 procedures per patient) [45]. As a supplementary analysis, we will perform ROC curves for repeated-measures design in each group (A and B) and compare them [46]. In addition, considering that the CPOT will be available in Group A and Group B, ROC curves will be performed in each group separately to compare the AUC of independent curves for each of the 2 procedures [45]. The NOL cutoff value that will optimize both sensitivity and specificity will be determined.

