### Methodological Strengths

The selection of rigorous validation strategies according to methodological guidelines in health measurement is the main strength of this study. With the participation of conscious ICU patients able to self-report, we can use the reference standard of pain, that is, self-reporting, for criterion validation. Furthermore, this validation strategy is reinforced by using the alternative reference standard, that is, the CPOT. Regarding discriminative validation, 2 strategies were selected, that is, discrimination between nonnociceptive and nociceptive procedures as well as before and after opioid administration. Test-retest reliability pre- and post-nonnociceptive and nociceptive procedures will allow us to examine the stability of the NOL values when patients are at rest. Both reliability and validation strategies are necessary to confirm the validity of an instrument [28].

In order to reduce potential bias related to pain scoring, Group A participants who are able to self-report will be blinded to the NOL values screen during the procedures. CPOT scoring will be completed by research staff before obtaining the patient’s self-report (ie, Group A participants) so raters are not influenced by self-reported pain intensity scores. Interrater reliability of CPOT scores will also be examined.

Our study lies in its foundation built upon the robust pilot work of the NOL conducted in the ICU setting. Our previous pilot studies have provided valuable insights and preliminary data to inform and support the research hypotheses and methodological decisions made in this study protocol. By expanding a rigorous validation process of the NOL to patients who are representative of the broader ICU population, the knowledge gained could contribute to identifying an alternative measure of pain in the most vulnerable critically ill adults.

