### Potential Limitations and Mitigation Strategies

Recruiting ICU patients or obtaining written consent from the persons qualified to consent for them is challenging. This requires daily screening of eligible patients and close follow-up. Support from the nursing staff and physicians is key to identifying eligible patients and approaching those qualified to consent for them. Our research team has developed efficacious recruitment procedures, trained competent research staff, and established close collaboration with ICU care teams in all sites, which facilitate the implementation of this study. The feasibility of recruitment was also demonstrated in our pilot work. A screening log will be completed at each site to compile eligibility criteria and reasons for refusals, losses, or withdrawals. In our pilot studies [26,27], we were unsuccessful in obtaining data from some participants mainly due to missing the procedure, either because temporary fellows forgot to inform the research team or the procedure occurred after ICU discharge. Chest tube removal and endotracheal suctioning were the sole nociceptive procedures included in our pilot studies. Broadening the selection of nociceptive procedures may reduce the number of missed observations of these events. However, we may still miss some procedures due to urgent situations. Also, data collection will be planned as soon as possible after obtaining written consent to minimize losses. In addition, we will document any challenges related to the use of NOL (eg, absence or loss of signal) and troubleshooting strategies. Finally, CPOT raters cannot be blinded to the procedures they will view on the videos. As a result, they may anticipate patients’ behavioral responses to the procedure, which may influence their ratings. The examination of interrater reliability of CPOT scores involving trained research staff from different settings and using 2 methods of rating (bedside and video) may help minimize this potential bias.

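### The NOL screen is turned away from patients and family, but nothing shields the bedside rater whose CPOT score is the only Group B reference standard

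*Protocol article*

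**What the plan says.** The shielding rule is in Study Procedures: "The screen of the NOL device is faced away from the patient and family members present in the room to reduce potential bias". In the same section, "the research staff sets up the NOL device at the bedside", and "CPOT assessments (one-minute observation or duration of the procedure) are performed on participants from Groups A and B by research staff". The description of the device adds that start and end times are entered on the monitor, "which is facilitated with the use of a wireless keypad". It does not name the operator.

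Data Analysis states: "CPOT scores will be obtained independently by 2 trained raters, one at the bedside and one who will view the patient videos". The purpose given for the video is "to allow for interrater reliability examination of CPOT scores with another trained research staff not present at the bedside". In Group B the ROC reference is CPOT above 2 and nothing else. In Group A the reference is self-report above 4, and CPOT-based curves are an addition.

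The Discussion lists the bias controls. Methodological Strengths says "Group A participants who are able to self-report will be blinded to the NOL values screen during the procedures", and adds that the CPOT is scored before the self-report is taken. Potential Limitations and Mitigation Strategies concedes that "CPOT raters cannot be blinded to the procedures they will view on the videos". Neither section mentions keeping NOL values from the CPOT rater.

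**The concern.** Criterion validation needs a reference standard scored without knowledge of the index test. The article accepts this for Group A, where it hides the NOL from the patients who produce the self-report. In Group B the patient produces no reference score; the bedside rater does. Turning the screen from the Group B patient and family therefore protects no reference measure, and the person who supplies it is not covered.

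A rater who can see the NOL while deciding between a CPOT of 2 and 3 may lean toward the monitor. Each such shift moves a patient to the side of the cutoff that agrees with the NOL, so the error favours the hypothesis. At stake is the Group B ROC analysis, which is part of the primary analysis, and to a lesser extent the additional CPOT curves in Group A.

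**Working it through.** **Step 1. Who is protected from what.**

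| Score | Produced by | Shielded from the NOL value? |
|---|---|---|
| Self-report, Group A | Patient | Yes (Study Procedures; Methodological Strengths) |
| CPOT at bedside, Groups A and B | Research staff | Not stated anywhere |
| CPOT from video, Groups A and B | Research staff not at the bedside | Likely, but not stated |

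The stated protection of CPOT raters is against the self-report. The conceded weakness is knowledge of the procedure. Neither concerns the NOL.

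**Step 2. Reproduce the plan's own figure.** Inputs from Sample Size Calculation for Group B: AUC 0.75 against 0.50, α .025, power 80%, pain to no pain 1.5:1, N = 50, so n1 = 30 and n0 = 20.

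- Null SE = √[(n1+n0+1)/(12·n1·n0)] = √(51/7200) = 0.0842.
- SE at 0.75 (Hanley-McNeil): Q1 = 0.75/1.25 = 0.600 and Q2 = 2(0.5625)/1.75 = 0.643. The variance is [0.1875 + 29(0.0375) + 19(0.0804)]/600 = 0.00467, so SE = 0.0683.
- Power, two-sided α .025: Φ[(0.25 − 2.241×0.0842)/0.0683] = Φ(0.898) = 81.5%.

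The smallest N reaching 80% is 49, against the stated 50. The sample size is not at fault.

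**Step 3. Illustrate the effect of exposure.** The document gives no rate at which a rater might be swayed. Assumptions: 60% of patients in pain, a binormal NOL, and an NOL cutoff that puts 60% of patients above it. When the NOL side and the unbiased CPOT class disagree, a fraction f of CPOT classes moves to the NOL side.

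For a NOL with no information (true AUC 0.50) this can be done by hand. The share above the NOL cutoff among patients labelled as in pain becomes (0.36 + 0.24f)/0.60 = 0.6 + 0.4f. Among those labelled as not in pain it becomes 0.24(1 − f)/0.40 = 0.6 − 0.6f. The AUC is 0.5 plus half the difference, that is 0.5 + 0.5f. The share of all ratings changed is 0.48f.

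Simulation with 1,000,000 draws gives:

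| True AUC | f = 5% | f = 10% | f = 20% |
|---|---|---|---|
| 0.50 | 0.53 | 0.55 | 0.60 |
| 0.65 | 0.67 | 0.69 | 0.72 |
| 0.70 | 0.71 | 0.73 | 0.76 |
| 0.75 | 0.76 | 0.78 | 0.80 |

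The first row agrees with the hand formula.

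**Step 4. Effect on the test at N = 50.** Using the Step 2 formula with the shifted AUC, the chance that an uninformative NOL gives a significant favourable result is 1.3% at f = 0, 2.6% at f = 5%, 4.8% at f = 10% and 13.8% at f = 20%.

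**Step 5. Would the planned reliability check reveal it?** Not dependably. Over f = 5-20%, the share of all ratings changed is 2.4-9.6% at a true AUC of 0.50 and 1.7-6.8% at 0.70. Agreement between the bedside and video raters can stay high with shifts of that size.

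**The case against.** The strongest reply is that this is silence in a condensed article. Screen position during scoring may be set out in a manual that is not shown. The text does not say that the rater looks at the monitor. Research staff is a collective term, and nothing says that the person running the device also scores the CPOT. All of this stands, and it makes the bias conditional. It does not remove the gap. The article chose to describe whom the screen faces away from and to list its rater controls and rater limitations, and this one is absent from each place.

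A second reply is that an independent video score is already planned. That helps, because it may supply an unexposed rating. However, no passage says that the display is out of frame or that video raters lack NOL data, and the article gives the video score only a reliability role. Which rater's score enters the ROC may be settled in an analysis plan that is not shown.

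A third reply concerns the illustration. The influence rates are assumed. The model also lets the rater react to the analysed NOL value, which is in fact a later average around the peak and not the live reading. Both criticisms are fair, so the figures show direction and plausible scale only.

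A reader might infer more than the document supports:

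- That the Group B AUC is biased. Exposure is permitted by the text, not stated.
- That Group A's main result is compromised. Its primary reference is self-report from patients who do not see the screen.
- That passing 0.75 would turn failure into success. The planned test is against 0.50, and 0.75 is the planning value.
- That the video score should simply become the primary reference. It shows only face and upper body, while the CPOT also rates body movements and muscle tension, and video may be declined.

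**Conclusion.** The gap is real and lies in the stated bias controls: no passage keeps the NOL value from the bedside staff who score the CPOT. It matters most in Group B, where the CPOT is the only criterion, and less for the additional CPOT curves in Group A.

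If the rater can see the NOL, the expected direction is upward. The size is unknown. With siding in 5-20% of discordant cases, an assumption and not a figure from the plan, a true AUC of 0.70 reads about 0.71-0.76 and one of 0.50 reads about 0.53-0.60. The point rests on the missing safeguard and on how easily it can be added, not on a demonstrated bias.

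**What to change.** 1. Turn or cover the NOL screen from the bedside CPOT rater during every scoring window, with signal checks made between assessments. NOL values are logged every 5 seconds and events are entered by wireless keypad, so data capture does not depend on watching the screen.
2. Keep the display out of the video frame and NOL data away from the video raters, and say so.
3. For patients already enrolled without this safeguard, pre-specify a sensitivity analysis that repeats the Group B ROC with the planned video rater's CPOT score, once confirmed NOL-blind.
4. State the residual risk in the limitations section.

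If bedside raters are already shielded in practice, one sentence saying so settles the point.

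The cost is a line in the procedures and a line in the analysis plan, with no additional rater. The downsides are that the signal is not watched during scoring, so a loss of signal may be noticed only afterwards, and that the video score covers only face and upper body and is missing where video was declined.

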### Study Rationale, Goal, Objectives, and Research Hypotheses

An instrument can only be shown as valid for a specific purpose in a given population and context [28]. The NOL index was initially developed and validated for nociception monitoring and related pain in anesthetized patients [17,19-25]. Therefore, validating its use for nociception (primary purpose) and pain assessment (related purpose) in critically ill adults admitted to the ICU (different population and context of care) is necessary. Inspired by our pilot work, strategies for this larger validation study include: (1) criterion validation (ie, NOL’s ability to detect pain according to pain standard criteria) and (2) discriminative validation (ie, NOL’s ability to discriminate between nonnociceptive and nociceptive procedures) [28]. Considering that reliability is a necessary condition for validity [28], test-retest reliability of the NOL’s ability to generate consistent values in similar conditions (eg, at rest) will also be examined.

Research Question: Is the NOL a valid method for the assessment of nociception and pain in critically ill adults in the ICU context?

In order to answer this research question, specific validation objectives are to examine the NOL’s ability to:

Detect pain in ICU patients able or not to self-report using appropriate pain standard criteria (ie, criterion validation);Discriminate between nonnociceptive and nociceptive procedures part of standard care as well as before and after the administration of a breakthrough opioid dose (ie, discriminative validation);Generate consistent values in similar conditions (ie, pre- and post-nonnociceptive and nociceptive procedures) when ICU patients are at rest.

Our research hypotheses to be tested include:

H1. The NOL index adequately classifies ICU patients with pain based on either their self-reported pain intensity or CPOT scores.

H2. The NOL index produces higher values during nociceptive procedures compared to nonnociceptive procedures and lower values post- versus preopioid administration.

H3. The NOL index generates consistent values pre- and post-nonnociceptive and nociceptive procedures when ICU patients are at rest.

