### Participants

A consecutive sampling method is used to approach all eligible patients or their representatives during the study period. This sampling method aims to capture a representative sample of ICU patients able or not to self-report. Eligible ICU patients (Textbox 1) are assigned to one of the following groups:

Group A can communicate their self-report of pain and can exhibit behaviors (conscious and alert with Glasgow Coma Scale [GCS] [30] score of 13 to 15 or Richmond Agitation Sedation Scale [RASS] [31] score of 0);Group B cannot communicate their self-report but can exhibit behaviors (altered level of consciousness with GCS score of 6 to 12 with a score ≥4 on the motor subscale or RASS score of –1 to –3); andGroup C cannot communicate their self-report or exhibit behaviors (unconscious with GCS score of 3 to 5 with a score ≤3 on the motor subscale or RASS score –4 or –5 or receiving neuromuscular blocking agents).

Exclusion criteria were selected to control for potentially confounding variables that may affect the NOL signal or pain standard measures. Patients assigned to Group A who screen positive for delirium are excluded as this condition is likely to affect the reliability of their self-report of pain [32]. Patients with conditions that may seriously influence perfusion of the hands, heart rate, heart rate variability, blood pressure, repetitive or high movements due to agitation or behavioral responses (eg, agitation, cognitive, or psychiatric conditions) are also excluded, thereby strengthening the internal validity of the study. Finally, patients with *Clostridium difficile* must be excluded because the required disinfection product (ie, sodium hypochlorite 5000-6000 ppm) could damage the NOL device, according to the manufacturer.

Eligibility criteria of intensive care unit (ICU) patients.

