#### Alternative Reference Standard Measure of Pain–Groups A and B

The Critical-Care Pain Observation Tool (CPOT) [13] was selected for behavioral pain assessment in critically ill adults. The CPOT was used in our NOL pilot studies [26,27], and it is 1 of the 2 behavioral scales suggested as alternative reference standard measures of pain by the Society of Critical Care Medicine [14] and has been implemented in clinical practice in the 3 study ICUs. The CPOT includes 4 behavioral items: (1) facial expressions, (2) body movements, (3) muscle tension, and (4) compliance with the ventilator (for mechanically ventilated patients) or vocalization (for nonintubated patients). Each item is scored from 0-2, and the total score can range from 0-8. The CPOT has been validated in 47 studies with more than 3900 ICU patients with surgical, trauma, and medical diagnoses from various countries [34]. Consistent findings of good interrater reliability (interclass correlation coefficient [ICC] >0.60 between research staff and ICU nurses) and ability to discriminate between various nociceptive and nonnociceptive procedures were found across studies. Criterion validation of the CPOT was also supported by positive correlations (*r*>0.40) with ICU patients’ self-reported pain intensity [34]. A CPOT score >2 was found to adequately identify patients with self-reported pain (AUC>0.80) [34,36].

The research staff of all sites have been trained to use the CPOT using a standardized training session previously described [37]. Briefly, this 60-minute training session covers the description of the CPOT content and its scoring process. Patient videos are viewed to practice scoring with the tool with the goal of reaching consistent CPOT scores between raters within a total score difference of no more than 1 point.

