### Sample Size Calculation

The primary objective is to validate the NOL using pain standard criteria (ie, self-report and CPOT scores). Therefore, ROC is considered our primary analysis and guides the sample size calculation for Group A and Group B. Power calculations were based on our pilot findings [26,27] and results from previous ICU studies considering a clinically acceptable AUC of 0.75 [42] (using a null hypothesis of AUC=0.50) with a power of 80% and an adjusted α of .025 (2 ROC curves for each procedure in each group). For Group A in whom the self-report of pain is obtained and using a ratio of 2:1 in pain:no pain cases according to self-reported pain intensity scores of <4 and >4, a sample of 54 patients is required. For Group B in whom only the CPOT scores are available and using a ratio of 1.5:1 in pain:no pain cases according to CPOT scores of <2 (no pain) and >2 (pain), a sample of 50 patients is necessary. For Group C (unable to self-report and express behaviors), we will not be able to use any pain standard criterion. Therefore, our main objective is to test whether the NOL can discriminate between a nociceptive procedure and a nonnociceptive procedure. In order to detect a minimal mean increase of 10 in the NOL value during the nociceptive procedure (with a standard deviation of 10 as found in our pilot findings), a minimal sample size of 13 patients is required to run paired *t* tests with a power of 80% and an α of .01 (to account for multiple test comparisons). Considering an attrition rate of 25% (data collection was completed in 73% of consenting patients in our pilot work), recruitment targets include 68 patients in Group A, 62 patients in Group B, and 16 in Group C for a total of 146 ICU patients. Power calculations were performed by a statistician using Power and Precision 4 (Biostat Inc).

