Discriminative validation (objective 2) is our main objective to test in Group C, and paired *t* tests comparing the NOL values of each nociceptive procedure with the nonnociceptive procedure will be obtained. Generalized linear mixed model for repeated measures will allow us to compare the NOL index values across time points (pre, during, and post), procedures (nonnociceptive vs nociceptive), and their interaction in each group (A, B, and C). The generalized linear mixed model technique incorporates the full-information maximum likelihood procedure, which allows parameter estimation for missing data [47]. NOL values are expected to be significantly higher during nociceptive procedures in all 3 groups. Covariates (eg, sex, gender, morphine equivalent doses, opioid use before ICU admission) may be added if appropriate. Finally, NOL data obtained at pre- and postadministration of an opioid dose will be tested separately using paired *t* tests as not all patients will be candidates for these assessments.

For test-retest reliability (objective 3), paired *t* tests will be performed between pre and post-nonnociceptive and nociceptive procedures in all 3 groups. Nonsignificant paired *t* tests are expected to support the stability of NOL values when the patients are at rest.

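### Bed turning is pooled with the other nociceptive procedures against comparators that do not move the body, so where turning is used the procedure part of H2 is partly a movement contrast; the key analyses should be repeated without it

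*Protocol article*

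**What the plan says.** Under Study Procedures, movement is given as a reason to restrict what is observed: "These procedures do not involve mobilizing the patient out of bed, as important movements may introduce artifacts in the NOL data". Under Participants, the conditions that lead to exclusion include "repetitive or high movements due to agitation or behavioral responses". The textbox of standard care procedures nevertheless names bed turning or repositioning among the nociceptive procedures. The choice follows clinical need: "Nociceptive procedures are selected according to the standard care required by the patient’s condition". Up to two are observed per participant, with no stated limit on how many may be turns.

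The nonnociceptive procedures are a one-minute touch of the arm and cuff inflation.

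The first part of H2 depends on this comparison: "The NOL index produces higher values during nociceptive procedures compared to nonnociceptive procedures and lower values post- versus preopioid administration". For Group C the Data Analysis section plans paired t tests "comparing the NOL values of each nociceptive procedure with the nonnociceptive procedure will be obtained". For Group B it plans one ROC curve per nociceptive procedure, two per patient, with CPOT above 2 as the criterion. Of that tool the article says "The CPOT includes 4 behavioral items: (1) facial expressions, (2) body movements, (3) muscle tension", the fourth item being ventilator compliance or vocalization.

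The NOL value analysed is a mean around the peak after the procedure starts. The stated safeguard is a check of signal quality for all enrolled patients.

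**The concern.** Turning is the one listed procedure that consists of moving the patient's body. When it fills a slot, the nociceptive and nonnociceptive conditions differ in two respects, noxious stimulation and movement, and the planned contrast cannot tell them apart. Turns enter the same slot as tube removal and suctioning, so the pooled estimate carries whatever movement adds. Taking the mean around the peak makes the measure sensitive to a brief upward disturbance, if there is one.

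Group C is most exposed. It has no self-report and no CPOT, and the article calls discrimination between procedures its main objective. A positive result there would be read as evidence that the index detects nociception in patients who cannot be assessed any other way.

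Group B is exposed by a different route. Its ROC curves are built within the nociceptive procedures, so soft touch and cuff inflation do not enter. The question is whether turning raises the CPOT through its body-movement item and also raises NOL. If it does, part of the AUC reflects shared movement.

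**Working it through.** **Inputs from the article (Sample Size Calculation, Data Analysis).** Group C: "minimal mean increase of 10 in the NOL value during the nociceptive procedure", SD 10, alpha .01, power 80%, n = 13. Group B: AUC 0.75 against 0.50, alpha .025, pain to no pain 1.5:1 (60% above the cutoff), n = 50.

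**The plan's own figures.**
- Group C, paired t test with standardized effect 10/10 = 1 and exact noncentral t. At n = 13, power is 80.6% with one-sided alpha .01 and 70.1% with two-sided. The stated 13 is reproduced as a one-sided calculation; the article does not state the sidedness.
- Group B, Hanley-McNeil variance and two-sided alpha .025. N = 49 is needed, and power is 81.5% at the stated 50.
- The Limitations section says the pilots covered only chest tube removal and endotracheal suctioning, so the pilot data behind the design contain no turning.

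**Assumed inputs.** The share of turns f and the upward artefact b in NOL points are not in the documents. The true nociceptive effect is set to zero.

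**Group C.** The mean difference produced by movement alone is f × b. With f = 0.5 this is 0.5 × 5 = 2.5 to 0.5 × 10 = 5 points, a quarter to a half of the 10-point design effect. The chance of a significant increase at n = 13, SD 10, two-sided alpha .01, by simulation:

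| Share of turns | b = 5 | b = 10 | b = 20 |
|---|---|---|---|
| 0 | 0.5% | 0.5% | 0.5% |
| 25% | 1.5% | 3% | 6% |
| 50% | 3% | 12% | 34% |
| 75% | 8% | 34% | 81% |
| 100% | 16% | 70% | about 100% |

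With one-sided alpha .01 the row for half turns becomes 6% (b = 5) and 19% (b = 10), against 1% with no turns.

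**Group B.** NOL is assumed to be unrelated to pain.
- If turning leaves the chance of CPOT above 2 unchanged (60% in both types, half turns, b = 10), the AUC is 0.50.
- If NOL and CPOT share a movement factor (correlation 0.2 to 0.4) in half the procedures, with no mean shift, the AUC is about 0.55 to 0.59. If the factor acts in all procedures, it is 0.59 to 0.68.
- If half are turns and CPOT positivity is 80% in turns against 40% in other procedures, the AUC is 0.61 (b = 10) to 0.68 (b = 20). With 90% against 30% it is 0.66 to 0.76. Only this last scenario, at b = 20, reaches the design value of 0.75.
- Each CPOT item scores at most 2 and the cutoff is above 2. The body-movement item alone therefore cannot make a patient positive; at least one further point must come from another item.

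**The case against.** The strongest reply is that the boundary is deliberate. The article says that important movements may cause artefact and draws its line at leaving the bed; in-bed turning lies on the permitted side. The Background names turning as a painful procedure, and the Limitations section says a broader list may reduce missed observations. This stands: there is a tension with the stated rationale, not a contradiction, and including turning is defensible.

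A reader might infer that H2 as a whole could be satisfied by movement, or that the procedure contrast is all the evidence Group C offers. Neither follows. H2 also requires lower values after an opioid, which turning cannot produce, and Table 1 records NOL before and after the analgesic in all three groups. That part is limited to patients who receive a breakthrough dose, so it does not replace the procedure contrast.

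A reader might also infer that the still comparators bias the Group B ROC. They are not in it. Nor does the article say that passive handling by staff scores CPOT points. A patient's own movement in response to pain is what the tool is meant to record, and muscle tension is not movement.

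Nothing says that artefact raises NOL. It could add noise or cause loss of signal, which would weaken the results. The device has an accelerometer and allows events to be annotated, and the full protocol or analysis plan may contain a motion rule. Its absence from an article is not itself a fault. What remains is the comparison the article does fix: turns pooled by slot against conditions without body movement.

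**Conclusion.** The concern holds in a limited form. Where turning fills a slot, the procedure part of H2 mixes nociception with movement, and the article's own rationale treats movement as a possible source of artefact. Group C matters most, because this contrast is its main test. In Group B the effect is possible but depends on turning raising both NOL and CPOT; without that the AUC is unaffected.

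The size cannot be determined from the documents. With half turns and an upward artefact of 5 to 10 points, Group C false positives rise from 0.5% to about 3% to 12%. With few turns the effect is small, and it becomes large only if turns dominate or the artefact exceeds the design effect. These figures rest on an assumed share, direction and size. They show what could happen, not that the result will be wrong. A cheap safeguard is justified; a change of design is not.

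**What to change.** Prespecify the procedure contrast of H2 in all groups, Group C first, and the Group B ROC, each with and without turning or repositioning. Report the number of turns by group and slot. Claim discrimination of nociception only if the estimate without turning is consistent with the full estimate in direction and size.

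If accelerometer data can be exported, add one motion rule for NOL windows, applied equally to rest, nonnociceptive and nociceptive windows, as a sensitivity analysis.

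The first step needs only the procedure type and data the study already collects. The cost is precision. If half of 13 Group C observations were turns, the standard error of the mean difference would rise from 10/√13 = 2.8 to 10/√6.5 = 3.9. Consistency should therefore be judged from the estimate and its interval, not from significance.

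Two other remedies are not recommended. Accepting turning only when nothing else is available departs from selection by care need and could bring back the missed observations that the broader list is meant to reduce. Removing the body-movement item from the CPOT shortens the 0 to 8 scale, so the cutoff above 2 would no longer apply as validated.
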